## Abstract

**Background:**

Motor milestones are not only indicators of developmental progress, but they also open up new opportunities for infants to interact with the environment and social partners, as the development of motor, social, and language skills is tightly interconnected in infancy. This study will investigate how the transition to independent sitting relates to key areas of socio-communicative development in infancy: vocal production and visual attention.

**Methods:**

This study addresses the relationship between sitting acquisition and social cognition skills in infancy. It will allow for comparing if infant motor development, vocalizations, and visual attention undergo developmental changes in parallel or whether they have intertwined trajectories. We will conduct a longitudinal study using a milestone-based approach to account for individual differences in relation to the timing of motor milestone acquisition. We will invite parent-infant dyads to the lab when infants are at different stages of independent sitting acquisition: non-sitting, attempting-sitting and expert-sitting. Infants’ attention toward faces and toys will be measured with a wearable eye-tracker during free-flowing dyadic interactions with their caregivers. During the same interactions, infant vocalizations will also be recorded and analyzed. Additionally, screen-based eye-tracking will be used to precisely assess changes in infants’ attention to the mouth area of the speaker.

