**Discussion:**

Altogether, this study will provide a unique dataset that tracks the cross-dependence of motor, visual and vocal developmental trajectories. It will have the potential to inform future studies of neurodevelopmental disorders such as autism that are characterized by socio-communicative challenges.

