### The current study

The acquisition of independent sitting transforms infant visual attention to faces [12, 15] in general but it is not clear whether it also contributes to the increase in visual attention to the mouth area as a source of audiovisual speech cues. The second related but unexplored issue concerns how the acquisition of sitting may alter the allocation of attention to speaking faces relative to other attractive visual objects during free-flowing social interactions. The proposed study, for the first time, combines the measurement of visual attention in a screen-based task with the measurement of attention during free-flowing social interaction in a design that tests their dependence on sitting acquisition. The acquisition of sitting potentially reorganizes multiple aspects of speech and face processing [52].

We aim to examine developmental trajectories in a cohort of infants with a low likelihood of ASD first to determine whether changes in vocal production and visual attention to faces occur simultaneously in relation to the acquisition of independent sitting. Understanding these trajectories first in typically developing infants will allow us to establish a baseline prior to any studies with EL-infants.

Pilot data collection and finalization of the study design were conducted between 13.07.2023 and 09.02.2024. The recruitment and data collection are ongoing. Data collection started on 16.02.2024. The data analysis has not started. The expected completion date of the recruitment is the end of August 2025.

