### Study objectives

#### Objective 1

To investigate how the transition to independent sitting changes infants’ visual attention to faces and toys during free play.

Prediction: Due to fewer postural constraints and less effort to maintain balance, infants, after learning to sit independently, would look longer at the caregiver’s face and toys than before acquiring this motor milestone [15, 17]. However, during the phase transition (attempting-sitting), infants’ look less toward faces and toys would be shorter than before and after the acquisition of sitting due to difficulties in maintaining a stable body position.

#### Objective 2

To investigate how the transition to independent sitting influences infants’ visual attention to mouth in a screen-based eye-tracking task.

Prediction: Increasing experience with viewing faces in an upright orientation, infants’ visual attention to the mouth while watching talking faces in a free-viewing task gradually increases as they gain sitting proficiency.

#### Objective 3

To investigate how the transition to independent sitting associates with infants’ vocal production.

Prediction: After learning how to sit independently, infants vocalize more and produce more advanced vocalizations (such as canonical babbling) than before acquiring this motor milestone [53, 54]. However, during the transitional phase (attempting-sitting), infants vocalize less due to difficulty in allocating attention to multiple tasks during the acquisition of a novel skill [50].

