### Statistical analyses

Data will be analyzed according to the aims of the study. The use of multiple eye-tracking methods in a single study may increase the risk of data attrition. Hence, we will adopt a flexible policy of participant inclusion on an analysis-by-analysis basis to maximize the sample size for each type of modeling. Thus, linear mixed models will be used to measure the effect of sitting expertise on each outcome variable. These models are suitable for longitudinal designs such as ours and for dealing with potential missing data. Infants’ age will be added to the analyses to control for the interaction between age-related and motor-development-related effects. The linear mixed models take into account the dependency and ordering of the data within subjects in repeated-measures designs. Moreover, even if a subject is missing one or more of the repeated measurements, the remaining data of that subject are used in the analysis.

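### Separate models for each outcome answer the three sitting objectives but cannot show whether vocal and visual trajectories are intertwined or cross-dependent

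*Protocol article*

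**What the plan says.** **The wider claim.** The Abstract (Methods) sets out to compare whether the three domains "undergo developmental changes in parallel or whether they have intertwined trajectories". The Abstract (Discussion) says the dataset "tracks the cross-dependence of motor, visual and vocal developmental trajectories". In the body, The current study aims to determine "whether changes in vocal production and visual attention to faces occur simultaneously in relation to the acquisition of independent sitting".

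**The objectives.** Study objectives lists three. The first is "To investigate how the transition to independent sitting changes infants’ visual attention to faces and toys during free play". The second relates sitting to mouth looking on screen, and the third relates sitting to vocal production. Each pairs sitting with one outcome domain.

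**The analysis.** Statistical analyses states that "linear mixed models will be used to measure the effect of sitting expertise on each outcome variable". On age it says: "Infants’ age will be added to the analyses to control for the interaction between age-related and motor-development-related effects". The sample follows a "flexible policy of participant inclusion on an analysis-by-analysis basis to maximize the sample size for each type of modeling". Nowhere does the article put a vocal and a visual measure in one model, use one to predict the other, or relate their changes within infants.

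**The concern.** The wider claim concerns how domains relate to each other. The stated analysis concerns how each domain relates to sitting stage, one at a time. A set of stage effects can say that looking and vocalising both change around sitting. It cannot say whether an infant who looks more than expected at a visit also vocalises more than expected at that visit, or whether change in one goes with change in the other.

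What is at stake is the interpretation. Similar stage curves for looking and vocalising fit two separate processes that each follow sitting, and they fit equally well two processes linked to each other. Without a planned joint analysis, any statement about cross-dependence between the vocal and visual domains would be unsupported, or would rest on an analysis chosen after the results were seen.

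**Working it through.** **1. The plan's own figure.** Sample size gives about 30 infants from a repeated-measures calculation with a moderate effect. The article does not give the other inputs, so I assume f = 0.25, alpha 0.05, correlation ρ = 0.5 between visits, sphericity, and m = 3 or 4 visits. The noncentrality is λ = f²·N·m/(1−ρ).

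- N = 30, m = 3: λ = 0.0625 × 30 × 3/0.5 = 11.25, power 0.84.
- N = 30, m = 4: λ = 0.0625 × 30 × 4/0.5 = 15, power 0.90.
- Smallest N with m = 3: 28 for 80% power, 31 for 85%.

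Over ρ from 0.3 to 0.5 and power from 0.80 to 0.95, N runs from 24 to 60. So about 30 is reproducible, but for a stage effect on one outcome. It does not cover an association between outcomes.

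**2. Why separate models are silent on coupling.** For infant i at visit j, write

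- looking: A = stage + age + u(A,i) + e(A,ij)
- vocalising: V = stage + age + u(V,i) + e(V,ij)

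Coupling lies in corr(u(A), u(V)) and corr(e(A), e(V)). The likelihood of A alone contains neither correlation, and nor does that of V alone. Two fits, one per outcome, therefore carry no estimate of either.

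**3. Illustration by simulation.** All values are assumed: 60 infants, 3 stages, 20% of visits missing independently per outcome, 200 replicates, uncorrelated infant intercepts, and a visit-level correlation of 0 or 0.6. Each outcome was fitted with stage, age and a random infant intercept.

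| True visit-level correlation | Expert vs pre-sitting, looking (SE) | Expert vs pre-sitting, vocalising (SE) | Within-infant residual correlation |
|---|---|---|---|
| 0 | 0.49 (0.46) | 0.47 (0.46) | 0.04 |
| 0.6 | 0.51 (0.46) | 0.50 (0.46) | 0.61 |

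The differences between rows in the stage effects are simulation noise: the Monte Carlo error of each mean is about 0.46/√200 = 0.03. The last column, which the plan does not compute, separates the two cases. The 0.04 is a small artefact of centring infants with missing visits.

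**4. What the data could detect.** Take 3 visits per infant and remove one degree of freedom per infant, two for stage and one for age. With the Fisher z approximation, two-sided alpha 0.05 and 80% power, r = tanh(2.80/√(df − 3)).

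- 60 complete infants: df = 180 − 60 − 2 − 1 = 117; r = tanh(2.80/√114) = 0.26.
- 30 complete infants: df = 90 − 30 − 2 − 1 = 57; r = tanh(2.80/√54) = 0.36.
- 60 infants with 20% missing per outcome (assumed): both outcomes at 0.8 × 0.8 = 64% of visits, or 115.2. Infants with at least one such visit: 60 × (1 − 0.36³) = 57.2. df = 115.2 − 57.2 − 3 = 55; r = tanh(2.80/√52) = 0.37.

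**The case against.** **The objectives are answerable.** All three relate sitting to one domain, and stage-plus-age models address them. This stands. A reader might infer that the study as planned cannot support its main purpose. The documents do not bear that out: only the further claim in the Abstract, and the vocal-visual aim in The current study, go beyond the models.

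**Intertwined may mean tied to sitting.** The section on tracking developmental transitions contrasts age-driven with posture-driven effects, and The current study asks about simultaneous change relative to sitting. On that reading, age-adjusted stage effects are relevant, and similar timing can be described from them. This stands for motor-to-vocal and motor-to-visual links. It does not reach the vocal-visual part of a claim that names three domains and their cross-dependence.

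**Differing samples.** A reader might infer from "flexible policy of participant inclusion on an analysis-by-analysis basis to maximize the sample size" that stage profiles cannot be compared across outcomes at all. That is too strong. The models come from one cohort, keep partly observed infants and, if data are missing at random, estimate means for the same cohort.

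**A visit-level correlation is not developmental coupling.** Face looking and vocalising are measured in the same interactions, so fussiness or fatigue on the day could correlate them. This stands, and the fix has to allow for it.

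**A fuller plan may add a joint model.** It may. The point here is not an omitted detail: the article states both the claim and the analysis meant to serve its aims, and the two do not match.

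**Conclusion.** The point holds, at moderate severity. The stated models serve the three sitting-to-outcome objectives. They cannot support the claims that the study separates parallel from intertwined trajectories or tracks cross-dependence between the vocal and visual domains, because no parameter in them links the two within infants. That conclusion follows from the form of the models and does not depend on the simulated values.

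This is a mismatch between claim and analysis, not a fault of design. The measures come from the same infants and visits, and the article says analysis has not started. Precision would be limited. The detectable correlation of 0.26 is a best case, since the article itself expects attrition and missing data. About 0.37 is more realistic if the assumed 64% of visits have both outcomes, and 30 complete infants give much the same (0.36).

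**What to change.** Before analysis starts, do one of the following.

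1. **Add a prespecified secondary joint analysis.** Fit a bivariate mixed model for each of two pairs: face looking with vocalising, and mouth looking with vocalising. Put stage and age in both equations, allow correlated infant effects and correlated visit-level residuals, and fit by likelihood on all available data. Report the within-infant association with its confidence interval. State that a same-session correlation may partly reflect the infant's state. Require support from the mouth-looking pair (a separate task), or from an association across successive visits, before calling it developmental coupling. State the detectable correlation as about 0.26 with 60 complete infants and about 0.37 under the 64% assumption.
2. **Narrow the claim.** Reword the Abstract (Methods and Discussion) so that it promises only the three sitting-to-outcome objectives, and present any comparison of stage profiles across domains as descriptive.

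The first option costs analysis text, code and some simplicity, and its estimates will be imprecise. The second costs wording only, but gives up the cross-domain question. Neither changes recruitment, visits or measurements.

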**Discussion:**

Altogether, this study will provide a unique dataset that tracks the cross-dependence of motor, visual and vocal developmental trajectories. It will have the potential to inform future studies of neurodevelopmental disorders such as autism that are characterized by socio-communicative challenges.

## Introduction

Neurodevelopmental conditions such as autism spectrum disorder (ASD) are often characterized by socio-communicative challenges (e.g [1–3]). One of the early differences in the context of socio-cognitive and communicative development is visual attention to faces. Chawarska et al. [4] and Jones et al. [5] found that six-month-old infants at elevated likelihood for ASD (with an older sibling with autism, EL-infants) – who eventually developed the condition themselves – tended to look less at the face of a speaker than those who did not, and compared to low-likelihood infants (LL-infants). Shic et al. [6] replicated this finding, but again only for speaking faces, not silent ones. Results from a study on infant-parent interactions showed that, regardless of later diagnosis, EL-infants, at a group level, looked less often at their parents’ faces than LL-infants [7]. In contrast, Elsabbagh et al. [8] found *increased* visual attention to faces presented on a screen in EL-infants as a group, irrespective of their later autism diagnosis, compared to LL-infants. Furthermore, a live eye-tracking study found that infants with and without a subsequent autism diagnosis differ very little in how much they look toward faces overall [9]. These puzzling differences indicate that the developmental variability in visual attention to faces – especially in naturalistic social interactions – is not yet fully understood, either in autism or in typically developing infants [10]. Moreover, some results from screen-based experiments, which limits ecological validity, may not reflect infants’ visual attention during real-life social interactions (see discussion in [11]), Importantly, visual attention to faces can also be linked to changes in gross motor development.

### Acquisition of sitting skills in relation to visual attention and vocal production

One of the key gross motor achievements changing the visual perspective of young infants is the developmental ability to sit independently [12, 13]. Infants usually start sitting independently between 5 and 8 months of age, with large disparities in the time of its onset (WHO Motor Development Study [14]). While sitting, infants are more likely to have toys in their view [12, 15], and they are also more in the center of their field of view [12, 16]. Similarly, sitting infants are more likely to see a caregiver’s face [15, 17], and the episodes of parent-infant mutual gaze and joint attention also happen more often when infants sit [17]. The caregivers are more likely to provide opportunities for learning when infants are sitting independently than when they are in other positions [13]. Interestingly, there are differences in how caregivers play with infants depending on their sitting proficiency. Supported sitting provides infants less of a boost to cognitive opportunities than independent sitting, potentially due to the fact that when caregivers provide postural support, they are likely to be positioned behind their infants, decreasing chances for face-to-face engagement and joint attention [13]. Accessibility of important social information from caregivers’ faces is easier during face-to-face play than during supported sitting [18].

Sitting has since long been postulated to relate to advances in vocal development. Yingling [19] documented significant associations between the onset of unsupported sitting and advances in consonant-vowel vocalizations in the first year of life, which are important precursors to speaking first words. Gallen et al. [20] reported that more advanced gross motor skills are linked to more advanced prelinguistic development and social development. Similarly, positive associations between gross motor and communication development were found in very preterm infants, with higher expressive language scores and more vocal production characterizing infants mastering unsupported sitting [21]. Furthermore, the earlier-than-average development of sitting skills (from 3 to 5 months of age) was predictive of subsequent higher receptive language scores at later time points (at 10 and 14 months of age), even while controlling for overall gross motor development [22]. However, it is unknown whether the acquisition of independent sitting skills is related to advances in infants’ vocal production.

### Acquisition of sitting skills in relation to visual attention to mouth

Screen-based eye-tracking research showed that the way in which infants focus on different facial areas (eyes, mouth) seems to undergo significant changes around the age when they start sitting independently. Infants’ visual attention to the articulating mouth increases between 4 and 8 months of age [23–27] as it provides audio-visual speech cues, which are highly relevant for acquiring phonetic, phonological, and vocabulary skills [27–30]. It has also been hypothesized that this increase in visual attention to the mouth may also be related to vocal development [23, 31], as infants use visual speech cues of talking faces as feedback for their own speech production.

### Consequences of delays in motor development for socio-communicative skills

Due to these important cascading effects on socio-communicative skills, delayed acquisition of sitting can have then crucial consequences for overall child development. Delayed acquisition of independent sitting might be an indicator of atypical development, but it is a sign of disintegrity of the developing system and not a condition-specific marker. For example, children with cerebral palsy (e.g [32]). Down syndrome (e.g [33]), and Rett syndrome (e.g [34, 35]), as well as infants who later receive an ASD diagnosis (e.g [36, 37]), might exhibit delays in sitting acquisition. Even though the delayed sitting acquisition is not the earliest marker of motor atypicality (earlier ones include, for example, differences in general movement patterns, maintaining stable head position, delayed acquisition of rolling from prone to supine and supine to prone, e.g [38–40], it is one of the red flags that parents can easily identify themselves and seek professional assessment and support. It is especially important in the case of neurodevelopmental conditions that usually get diagnosed later in toddlerhood or early childhood but could hugely benefit from early identification and intervention or professional support, such as ASD [41]. Even though postural deficits are not a primary diagnostic criterion for ASD, evidence suggests that they are part of the overall prodromal ASD profile (see [42–45] for reviews). Concerns related to the motor domain are also reported by parents of EL-infants (e.g [46]).

### Tracking developmental transitions of multiple skills

As each new posture is initially unstable (as measured behaviorally or kinematically) and requires practice (involving multiple failed attempts), it is important to track changes across the process of learning a new motor skill. For example, expert-sitters can adapt their postural control to maintain balance on both compliant and firm surfaces [47], but similar variability can be difficult for infants who just started to sit independently (new-sitters). For them, the challenge of staying upright takes a lot of attentional resources, minimizing their engagement in other behaviors, such as reaching for objects [48, 49]. New-sitters, during their first attempts, need to learn how to maintain their balance to avoid falling and adjust the coordination of the upper limbs with the demands of sitting upright (e.g [37]).,. Once the novel skill is mastered, it requires less attentional resources and allows for the simultaneous performance of other actions [50]. Thus, behavioral flexibility increases with sitting experience [51].

In this study, we align the testing schedule with the onset of independent, arms-free sitting rather than chronological age in order to explore how visual attention and vocal production change across the process of learning a new motor skill. We will control for chronological age, but the milestone-based approach aims to account for individual differences in the timing of sitting acquisition. Recently, Gallen et al. [20] showed that age-adjusted relative advances in motor development are linked to concurrent prelinguistic and social development, supporting the idea of developmental interaction across neurocognitive domains. In this study, we aim to capture such developmental interactions across neurocognitive domains but center them around a specific motor milestone to better understand the age-driven vs. posture-driven effects.

### The current study

The acquisition of independent sitting transforms infant visual attention to faces [12, 15] in general but it is not clear whether it also contributes to the increase in visual attention to the mouth area as a source of audiovisual speech cues. The second related but unexplored issue concerns how the acquisition of sitting may alter the allocation of attention to speaking faces relative to other attractive visual objects during free-flowing social interactions. The proposed study, for the first time, combines the measurement of visual attention in a screen-based task with the measurement of attention during free-flowing social interaction in a design that tests their dependence on sitting acquisition. The acquisition of sitting potentially reorganizes multiple aspects of speech and face processing [52].

We aim to examine developmental trajectories in a cohort of infants with a low likelihood of ASD first to determine whether changes in vocal production and visual attention to faces occur simultaneously in relation to the acquisition of independent sitting. Understanding these trajectories first in typically developing infants will allow us to establish a baseline prior to any studies with EL-infants.

Pilot data collection and finalization of the study design were conducted between 13.07.2023 and 09.02.2024. The recruitment and data collection are ongoing. Data collection started on 16.02.2024. The data analysis has not started. The expected completion date of the recruitment is the end of August 2025.

